#### Procedure completion rate

Procedure completion rate (with the Clopper-Pearson exact 95% confidence interval) will be estimated for each group in the FAS. The chi-square test will also be conducted and the odds ratio (with 95% confidence interval) will be calculated to evaluate the between-group differences in procedure completion rates. The adjusted odds ratio (with 95% confidence interval) will be calculated using logistic regression analysis including the assignment factors.

#### Sample cellularity

Sample cellularity will be tabulated by grade for each group in the FAS. The chi-square test will also be conducted to evaluate the between-group difference in tissue sampling rate. The adjusted odds ratio (with 95% confidence interval) will also be calculated using a proportional odds model including the assignment factors.

#### Incidence of complications

The incidence of complications (with the Clopper-Pearson exact 95% confidence interval) will be estimated for each group in the FAS. The chi-square test will also be conducted and the odds ratio (with 95% confidence interval) will be calculated to evaluate the between-group differences in the incidence of complications. The adjusted odds ratio (with 95% confidence interval) will be calculated using logistic regression analysis including the assignment factors.

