### Analysis target group

In the effectiveness analysis population, the full analysis set (FAS) is the main analysis and the per-protocol set (PPS) analysis is performed as a reference. In the safety analysis target population, all test samples are analyzed.

The FAS is defined as all registered cases excluding those who do not meet the eligibility criteria of this study after registration. The safety analysis target population is defined as cases who received part or all of the protocol treatments among all registered cases. The PPS is defined as cases excluding those meeting the following criteria from the FAS:
Inability to evaluate efficacy due to inadequate observationCritical deviation violating the specifications of the protocol

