#### Procedure completion

It is not necessary to use the same needle for subsequent punctures. The operator may freely select the puncture needles for subsequent punctures depending on the size and number of specimens obtained during the first puncture. In this study, only the specimen obtained with the first puncture will be used to evaluate the pre-specified outcomes. The EUS-FNA procedure will be considered complete when the operator determines that sufficient specimens have been collected at the second or subsequent punctures.

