### Safety analysis

The severity of adverse events will be graded according to the guidelines issued by the American Society for Gastrointestinal Endoscopy [12]. The incidence rate and proportion of adverse events during follow-up will be calculated for the safety analysis set, both overall and stratified by severity. Clopper-Pearson exact 95% confidence intervals will be estimated for these occurrence proportions.

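### The only stated comparison of complications between needles is set in the FAS, not in the safety population that the plan itself defines

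*Protocol article*

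**What the plan says.** Three places in the protocol article bear on this point.

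- **Analysis target group.** The FAS has an efficacy role: "In the effectiveness analysis population, the full analysis set (FAS) is the main analysis". It is defined by eligibility alone: "The FAS is defined as all registered cases excluding those who do not meet the eligibility criteria of this study after registration". Safety has its own set, defined by treatment: "The safety analysis target population is defined as cases who received part or all of the protocol treatments among all registered cases".
- **Incidence of complications**, under Secondary efficacy analysis: "The incidence of complications (with the Clopper-Pearson exact 95% confidence interval) will be estimated for each group in the FAS". The chi-square test and odds ratio are then given "to evaluate the between-group differences in the incidence of complications", followed by an adjusted odds ratio.
- **Safety analysis**: "The incidence rate and proportion of adverse events during follow-up will be calculated for the safety analysis set, both overall and stratified by severity". Exact confidence intervals are planned there, but no test or effect measure comparing the needles is stated.

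The Outcomes section lists complications as the fourth secondary endpoint, and Study aims and design names safety as one of the two things on which the needles are compared.

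**The concern.** Complications of a puncture are a safety outcome, and the plan's own rule is that safety is analysed in those who were treated. The complications paragraph departs from that rule without giving a reason. Because the safety section states no comparison between needles, this paragraph supplies the trial's whole stated safety contrast.

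The two sets differ in both directions. A patient who was punctured and afterwards found ineligible is in the safety population but not in the FAS, so a complication in that patient would not enter the needle comparison. An eligible patient who was registered but never punctured is in the FAS and adds to the denominator without having been exposed to either needle. At stake is whether the reported complication rates, and the odds ratio between needles, describe the patients who were exposed to them.

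**Working it through.** **1. Membership of the two sets, from the definitions**

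| Patient | FAS | Safety population |
|---|---|---|
| Eligible, punctured | in | in |
| Found ineligible after registration, punctured | out | in |
| Eligible, no protocol treatment | in | out |
| Found ineligible, no protocol treatment | out | out |

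The sets disagree in the second and third rows.

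**2. The plan's own numbers**

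Inputs from Sample size calculation: 75% against 85% correct diagnosis, two-sided α = 0.05, power 80%, chi-square test. With pooled variance and no continuity correction:

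n = [1.960 × √(2 × 0.80 × 0.20) + 0.842 × √(0.75 × 0.25 + 0.85 × 0.15)]² / 0.10² ≈ 250 per arm.

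This reproduces the stated 250. Adding the stated allowance of about ten ineligible patients per group gives 260. That allowance is the only guide in the document to how far the two sets may differ: 10/260 = 3.8% per arm. It is an upper guide, because not all of those patients need have been punctured.

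**3. Expected number of events lost from the comparison**

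The document gives no complication rate, so 2% and 4% are assumptions. Suppose all ten excluded patients per arm were punctured and carry the same risk p as the others.

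- Expected loss = 10 × p: 0.2 events at 2%, 0.4 events at 4%.
- Chance of losing at least one event = 1 − (1 − p)¹⁰: about 18% at 2%, about 34% at 4%.
- Chance of losing at least two = 1 − (1 − p)¹⁰ − 10p(1 − p)⁹: about 1.6% at 2%, about 6% at 4%.

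**4. What a lost event would do to the rate in one arm**

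Clopper-Pearson 95% intervals, with 250 in the FAS and 260 in the safety population (all ten ineligible patients punctured, no eligible patient left untreated):

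| FAS | No event lost | One event lost | Two events lost |
|---|---|---|---|
| 2/250 = 0.80% (0.10–2.86) | 2/260 = 0.77% (0.09–2.75) | 3/260 = 1.15% (0.24–3.33) | 4/260 = 1.54% (0.42–3.89) |
| 5/250 = 2.00% (0.65–4.61) | 5/260 = 1.92% (0.63–4.43) | 6/260 = 2.31% (0.85–4.95) | 7/260 = 2.69% (1.09–5.47) |
| 12/250 = 4.80% (2.50–8.23) | 12/260 = 4.62% (2.41–7.92) | 13/260 = 5.00% (2.69–8.40) | 14/260 = 5.38% (2.97–8.87) |

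The change of denominator alone hardly matters. One lost event moves the rate by a few tenths of a percentage point, well inside the confidence interval.

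**The case against.** The best defence is that little is lost. The safety section still records adverse events in every treated patient, by severity and with exact intervals, so harm to punctured but ineligible patients will be reported. Registration of candidates withholds a registration number until eligibility is confirmed, and Observation requires a Doppler check of the puncture route. Few patients should therefore be punctured and then found ineligible. One may add that an FAS comparison stays close to the groups as allocated. All of this stands, and it limits the size of the problem. It does not remove the inconsistency: the stated needle comparison is still made outside the set that the plan assigns to safety.

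A reader might infer more than the document supports:

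- *That the FAS leaves out the patients most likely to be harmed.* Bleeding tendency and an intervening vessel are exclusion criteria, but both are checked beforehand. Nothing in the document indicates that the later exclusions would be mainly such patients.
- *That a large share of the events would vanish.* Losing one or two events among ten patients implies a 10% to 20% risk in them, against the 2% to 4% assumed for the rest. That is a tail case, not the expected effect.
- *That two conflicting complication rates would be published.* The footnote to the data collection schedule defines adverse events to include those unrelated to the procedure. This outcome is broader than complications, so different figures would not by themselves conflict.
- *That mixed needle use is part of the same error.* Under Procedure completion, "The operator may freely select the puncture needles for subsequent punctures". This does blur which needle caused a complication, but it is an openly stated design feature, and a change of analysis set does not cure it.

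**Conclusion.** The point holds as an inconsistency over the analysis set. The complications paragraph puts the only stated between-needle comparison of complications in the set meant for effectiveness, contrary to the plan's own definition of a safety population and to its use in the safety section.

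Severity is low to moderate. The point concerns one secondary endpoint and at most about 3.8% of each arm, with an expected loss of 0.2 to 0.4 events per arm. Those figures assume that all ten excluded patients per arm were punctured and that their risk is the same 2% to 4% as the others'. If fewer were punctured the effect is smaller; if their risk is higher it is larger. The document settles neither. Nothing in it suggests that the mismatch would differ between arms, so no bias in the needle contrast is shown. The primary analysis and the sample size do not depend on this point.

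**What to change.** In Incidence of complications, replace the FAS with the safety analysis population, grouped by the needle used for the first puncture, for the incidence, the chi-square test and both odds ratios. Keep the FAS version as a supportive analysis. The sections Analysis target group, Incidence of complications and Safety analysis then agree. Make the change before the data are analysed, so that the set is not chosen with the results in view.

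The cost is a change of wording and one repeated table. The safety population is already defined, and no further patients are needed. A table splitting complications by whether another needle was used in later passes would be a useful option, but it is not needed to correct this point.

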### Setting

A total of 520 patients will be recruited from 21 endoscopic centers in Japan.

Registration will be performed at each participating center following local ethics committee approval of the study protocol and of the informed consent documentation and forms.

### Eligibility criteria

The following inclusion criteria will be applied: (i) age ≥ 20 years; (ii) pancreatic mass lesion detected on diagnostic imaging; (iii) performance status ≤ 2; (iv) indication for histological evaluation to predict the clinical course and to select treatment methods; (v) written consent obtained following adequate explanation of the study aims, design, and procedures.

The following exclusion criteria will be applied: (i) blood vessel or other tumors located between the lumen of the gastrointestinal tract and the target lesion; (ii) bleeding tendency, defined as an international normalized ratio of the prothrombin time > 1.5 or platelet counts < 50,000 cells/μl; (iii) any condition expected to hinder endoscope insertion; (iv) gastrointestinal reconstruction after gastrectomy; (v) serious complication involving another organ; (vi) known diffuse autoimmune pancreatitis; (vii) any other condition or situation determined by a study investigator to represent reason for ineligibility.

### Registration of candidates

At each participating center, the on-site study investigators will obtain informed consent from the candidates and use an electronic data capture system to confirm that the candidates meet the eligibility criteria (i.e., the candidates meet all the inclusion criteria and none of the exclusion criteria), input the necessary information, and register the candidates with the registration secretary. After confirming that the candidate meets the criteria, a registration number will be issued, and the registration will be considered complete. If any required input data are missing or the candidate does not meet the eligibility criteria, no registration number will be issued, and registration will be deemed incomplete. For each candidate, the date of registration is defined as the date when the registration number was issued by the registration secretariat via the electronic data capture system.

### Treatment allocation and blinding

Each subject will be assigned to either of the treatment methods at a ratio of 1:1 according to a web-based registration program system (based on dynamic allocation by the minimization method). Dynamic allocation by the minimization method is designed to minimize imbalance between treatments taking stratification factors into account. For assignment to prevent large bias. Based on the baseline factors for treatment allocation, including the diameter of tumor, site where the tumor is located, pattern of contrast computed tomography, and institution, an imbalance score is computed. The treatment with the lowest imbalance score is assigned.

The registration secretary will strictly control the program to prevent leaking of the assignment information. Blinding will not be used in this study.

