### Histopathological diagnosis

Histopathological diagnosis will not be based on cytology but on histology. Specimens fixed with formalin will be embedded in paraffin blocks. Immunostaining and nuclear staining will be performed as needed. In this study, the specimens obtained at the first puncture will be sent to Hoken Kagaku West Japan Co., Ltd, who will prepare the specimens and send them to Kyoto Prefectural University of Medicine for diagnosis. Two experienced pathologists who have performed at least 1000 cytology and histology evaluations of EUS-FNA specimens will assess the specimens independently. The two pathologists will be blinded to the type of needle used. Histology evaluation will be performed to determine: (i) sample cellularity, (ii) preservation of tissue architecture, and (iii) histologic diagnosis. Sample cellularity is classified as rich (≥ 5000 cells), moderate (100–5000 cells), or poor (< 100 cells).

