## Discussion

The choice of the most suitable needle for the diagnosis of pancreatic masses remains controversial. Several factors may affect the results of EUS-FNA biopsy, including the nature of the target lesion, the experience of the endoscopic expert, the type of needles used, the number of needle passes, and the availability of an on-site cytologist or pathologist. Moreover, specimen processing can vary between institutions, which may be a particularly relevant confounder for the diagnostic ability of EUS-FNA because the specimen collected via needle aspiration is minute. One important advantage of our study is that all samples analyzed are first-pass samples obtained using the same procedure and subjected to histologic analysis in a single facility staffed by experienced pathologists. Furthermore, the study design prevents selection bias because candidates will be recruited from among consecutive patients indicated for EUS-FNA. Finally, the study design prevents information bias because the pathologists will be blinded to the type of needle used.

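### Minimisation is stated without a random element, on institution and unblinded, so staff can guess the next needle better than chance; consecutive recruitment does not prevent the resulting risk of selection bias

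*Protocol article*

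**What the plan says.** All references are to the protocol article.

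- **Treatment allocation and blinding.** Each subject is "assigned to either of the treatment methods at a ratio of 1:1 according to a web-based registration program system", using dynamic allocation by minimisation. From baseline factors "including the diameter of tumor, site where the tumor is located, pattern of contrast computed tomography, and institution, an imbalance score is computed", and then "The treatment with the lowest imbalance score is assigned". No assignment probability, factor weights, factor levels or tie rule are given.
- **Same section, safeguards.** "The registration secretary will strictly control the program to prevent leaking of the assignment information". Also: "Blinding will not be used in this study".
- **Registration of candidates.** On-site investigators obtain consent, confirm eligibility and register the patient.
- **Eligibility criteria.** The last exclusion is open-ended: "any other condition or situation determined by a study investigator to represent reason for ineligibility".
- **Histopathological diagnosis.** "The two pathologists will be blinded to the type of needle used".
- **Discussion.** It states that "the study design prevents selection bias because candidates will be recruited from among consecutive patients indicated for EUS-FNA".

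**The concern.** Under the rule as worded, chance enters only when the two scores tie. Otherwise the next arm follows from past allocations and the new patient's factor levels. Institution contributes to the score, and staff see every needle used at their own centre, so they hold part of the information that fixes the next assignment. The same staff decide whom to register and when, under an exclusion that leaves room for judgement.

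The safeguard on the program protects the program. It does not stop staff inferring the next arm from what they have already seen. Blinded pathologists protect the reading of specimens, not enrolment. Consecutive recruitment governs who is approached; it does not remove foreknowledge of the arm.

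At stake is the primary comparison of diagnostic accuracy. If lesions that are easier to sample were enrolled more readily when one needle was expected, the arms would differ for reasons other than the needle.

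**Working it through.** **1. The plan's own figure.** The article gives no figure for predictability. Its sample size gives the scale of the planned effect. Inputs (Sample size calculation): 75% against 85%, two-sided α = 0.05, power 80%, chi-square test.

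n per arm = [1.960·√(2·0.80·0.20) + 0.842·√(0.75·0.25 + 0.85·0.15)]² / 0.10² ≈ 250.

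This reproduces the stated 250 per group. The planned effect is 10 percentage points.

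**2. How well can staff guess?** From the article: 520 patients, 21 centres, four minimisation factors including institution, lowest score assigned, open label. Assumed, because the article does not give them: two levels for each of the other three factors, or two, three and three; institution weighted 1, 2 or 4 relative to the others; imbalance measured by range or by squares; ties broken at random; equal-sized centres. Sixty simulated trials were run per setting.

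Guessing rule: name the needle used less often so far at one's own centre, and toss a coin when the counts are equal. Staff need no knowledge of other centres.

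| Rule | Institution weight | Correct overall | Correct when centre counts unequal |
|---|---|---|---|
| Lowest score assigned (as stated) | 1 (equal) | 64-65% | 71-73% |
| Lowest score assigned | 2 | 69-71% | 83-88% |
| Lowest score assigned | 4 | 73-75% | 94-100% |
| Favoured arm with probability 0.8 | 1 (equal) | 59% | 62-63% |
| Favoured arm with probability 0.8 | 4 | 65-68% | 72-80% |
| Simple 1:1 randomisation | – | 50% | 50% |

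A separate simulation with 21 unequal centres and equal weights gave 64.2-64.8% overall and 71.5-72.5% when unbalanced. With probability 0.8 it gave 58.5-59.1% and 61.2-62.3%.

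**3. What guessing could do to the result (illustration only).** Let g be the proportion of correct guesses. Let d be the difference in correct-diagnosis rate between lesions enrolled when the Franseen needle is expected and lesions enrolled when the conventional needle is expected. The Franseen arm then has a fraction g of the former, and the conventional arm 1 − g, so

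spurious difference = g·d − (1 − g)·d = (2g − 1)·d.

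Take g = 0.645 and an assumed d of 10 points, with every guess acted on: 0.29 × 10 = 2.9 points, against a planned effect of 10. With 250 per arm at 75%, the standard error is √(2·0.75·0.25/250) = 0.0387, so the shift is 0.029/0.0387 = 0.75 standard errors. The two-sided type I error becomes P(Z > 1.96 − 0.75) + P(Z < −1.96 − 0.75) ≈ 12% instead of 5%. With g = 0.59 the spurious difference falls to 0.18 × 10 = 1.8 points. The document supports neither the value of d nor the assumption that guesses are acted on; both are worst-case inputs.

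**4. Could predictable assignments simply be excluded?** Let u be the share of patients who enter when their centre's counts are unequal. Overall accuracy is u·(accuracy when unequal) + (1 − u)·0.5. With 0.652 and 0.730, u = 0.152/0.230 = 66%. Excluding these patients leaves about 0.34 × 520 ≈ 177, or about 88 per arm. Power for 75% against 85% is then Φ[(0.10 − 1.96·√(0.32/88))/√(0.315/88)] ≈ 38%. Such an analysis could not confirm or refute the main result.

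**The case against.** - **The sentence may be shorthand.** A journal article condenses the full protocol, and weights, tie rules and assignment probabilities are often left out, partly so that sites cannot guess. The article cannot settle whether its sentence is the complete rule. This stands as a caveat. But the article states a rule rather than staying silent, and if the program differs, the sentence is wrong and needs correcting.
- **Staff cannot know the next needle.** A reader might infer that they can, or cite the simulated result that about 80% of assignments are fully determined. The documents do not support that. The 80% applies only to someone who sees all centres' totals on all four factors. With equal weights, staff relying on their own centre's counts are wrong about one time in three.
- **Bias is not shown.** Someone would have to act on the guess by departing from consecutive recruitment or misusing a routine exclusion clause. This stands: nothing in the article shows that anyone did.
- **Much of lesion difficulty is already handled.** Diameter, tumour location and CT pattern are minimisation factors. Reading the site excluded under Major analysis and judgment criteria as the institution, they also enter the Mantel-Haenszel stratification and the adjusted logistic model. Steering on them is therefore largely balanced and adjusted for. This stands, and confines the risk to other features, such as ease of puncture.
- **The Discussion sentence may concern only who enters the study.** On that reading it is defensible, but as written it says that the design prevents selection bias, without that limit.
- **It may be too late to change the rule.** Trial status expected enrolment to be complete by November 26, 2019. This stands and shapes the fix.

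**Conclusion.** The point holds as a documented design weakness and an overstated claim. The allocation rule as published, with institution as a factor and no blinding, lets centre staff guess the next needle about 64-65% of the time from their own history, and 71-73% when the centre's counts are unequal, against 50%. The figures rest on equal factor weights and two to three levels per factor; extra weight on institution raises them to as much as 75% and 94-100%.

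The consequence is a risk of selection bias on features other than the minimisation factors. It is not proof of bias and does not invalidate the trial. The 12% type I error is an upper-end illustration under assumed full steering, not an estimate. Consecutive recruitment, control of the program and blinded reading do not remove the risk, so the Discussion's claim should be narrowed.

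**What to change.** 1. **If patients are still to be enrolled:** assign the arm with the lowest imbalance score with a probability below 1. A value of 0.8 is one example; with equal weights it lowers own-centre guesses to about 59%. This is one parameter in the web program. The sample size is unchanged; the cost is slightly larger chance imbalance in the factors, handled by adjusting for them.
2. **If the program already has a random element:** correct the sentence in Treatment allocation and blinding to say so. This is a change of wording only.
3. **If enrolment closed under the stated rule:** limit the Discussion's claim to who is approached for the study, acknowledge the predictability of allocation as a limitation, and report baseline lesion features by arm. This needs only text and a baseline table.

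Do not add a sensitivity analysis that excludes predictable assignments: it would keep about a third of the patients, with about 38% power.
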